**Methods and analysis::**

The Lung and Heart meridians are chosen as 2 specific studied meridians. 120 participants will be enrolled and divided into the healthy control group, chronic stable angina pectoris group and healthy intervention group. Laser doppler flowmetry will be used to assess the blood perfusion of the Heart and Lung meridians. The specificity for the meridian-visceral association will be investigated by comparing the microcirculatory difference between the Heart and Lung meridians in the healthy control group and chronic stable angina pectoris group. Besides, participants in the healthy intervention group will receive 2 sessions of moxibustion in the Heart meridian and Lung meridian, respectively, to explore the specificity for the site-to-site association on the body surface. Primary outcomes will be blood flow curve and blood perfusion units of relevant sites along the Heart and Lung meridians. Statistical analysis will be conducted by third party statisticians.

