**Figure 3 F3:**
[figure not shown]
The intervention procedure of the healthy intervention group. (A) Moxibustion site of the Heart meridian and LDF measurement sites of the Heart and Lung meridians; (B) Moxibustion site of the Lung meridian and LDF measurement sites of the Heart and Lung meridians. CSAP = chronic stable angina pectoris, LDF = laser doppler flowmetry.

(1)Intervention in the Heart meridian: By igniting the moxa stick and inserting it into a homemade moxibustion holder to adjust appropriate angle and height, moxibustion will be performed at “Shaohai” (HT3) of the Heart meridian for 15 minutes. During moxibustion, LDF probes will be placed in three measurement sites, which include the midpoint of the Heart meridian along the left forearm (ie, midpoint of between HT3 and HT7), “Chize (LU5)” of the Lung meridian, and the midpoint of the Lung meridian along the left forearm(ie, midpoint of between LU5 and LU9). The intervention procedure and LDF measurement sites are shown in Figure 3 (A). The measurement time points include 5 minutes before moxibustion, 15 minutes during moxibustion and 5 minutes after removal of moxibustion.(2)2)Intervention in the Lung meridian: The moxibustion acupoint is “Chize” (LU5) of the Lung meridian. The LDF examination, moxibusition procedure and measurement time points are the same as 1). During moxibustion, the LDF probes will detect the blood perfusion in three measurement sites, which include the midpoint of the Lung meridian along the left forearm(i.e. midpoint between LU5 and LU9), “Shaohai” (HT3) of the Heart meridian, and the midpoint of the Heart meridian along the left forearm (i.e. midpoint between HT3 and HT7. The intervention procedure and LDF measurement sites are shown in Figure 3(B).

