### Outcome measures

2.7

Primary outcomes include

(1)blood flow curve and(2)blood PU of relevant sites along the Heart and Lung meridians.

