### Data collection and statistical analysis

2.10

Statistical analysis will be performed using the statistical software package SPSS 17.0 for Windows (SPSS Inc., Chicago, IL) by third party statisticians who does not participant in this trial. Numeric data with normal distribution will be expressed as mean ± standard deviations, whereas data with skewed distribution as median with 95% confidence intervals. Categorical data will be shown as counts and percentages.

Repeated measures ANOVA will be used to assess change in continuous variables before and after intervention. The paired samples *t*-test will be used to compare the changes within the groups, whereas the independent samples t-test will be employed for comparisons between the groups. Within-group/between-group comparison regarding data with skewed distribution is assessed using non-parametric test. Between-group differences for baseline dichotomous variables, such as gender and ages, will be tested using the Chi-square test. A *P* value of less than .05 will be considered statistically significant.

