Second, our study design presents different comparisons to verify the specificity for the meridian-visceral association and site-to-site association between 2 specific meridians, which is a highlight. The theory of meridian-viscera association emphasizes the diagnostic and therapeutic values based on the mutual relation in physiology and the interaction effect in pathology between meridians and viscera. In details, visceral physiological functions and pathological changes will manifest in the corresponding meridians or the acupoints^[33]^ and the visceral disorders can be treated with the involved meridian and acupoints.^[34]^ A number of modern studies have confirmed the relatively specific relationship between meridians and viscera, and the modulating effect of acupoints/meridians for the visceral function^[35–37]^ On 1 hand, we hypothesize that the change in microcirculatory characteristics of the Heart meridian between the healthy control group and CSAP group is more significant than that of the Lung meridian. Thus, the specificity for the meridian-visceral association will be investigated by comparing the microcirculatory difference between the Heart and Lung meridians in the healthy control group and CSAP group. We present such a comparison (healthy control group vs CSAP group) to verify the sensitization phenomena of meridians under pathological circumstances as well as the specificity of meridian-visceral association.

On the other hand, we hypothesize that the change in microcirculatory characteristics in relevant sites of the stimulated meridian is more significant than that of the non-stimulated meridian in the healthy control group. Thus, the specificity for the site-to-site association will be explored by comparing the microcirculatory change between the Heart and Lung meridians by performing moxibustion in the Heart meridian and Lung meridian, respectively. It should be noted that moxibustion intervention is applied only in the healthy control group rather than the CSAP group. By such a study design and comparison, we attempt to confirm whether meridians are not only sensitized in pathological conditions but also activated in physiological state, which is an important issue to be solved in meridian researches.

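### Two primary outcomes at unspecified sites are all judged at P<.05, and no planned test is tied to the two Heart-versus-Lung hypotheses

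*Protocol article*

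**What the plan says.** The Abstract of the protocol article states: "Primary outcomes will be blood flow curve and blood perfusion units of relevant sites along the Heart and Lung meridians". Section 2.7 repeats this as two numbered primary outcomes, the second being "blood PU of relevant sites along the Heart and Lung meridians". Neither place says which sites are relevant or how a curve becomes an analysable value.

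Section 2.6.1 fixes what is recorded:

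- **Healthy controls and chronic stable angina pectoris (CSAP) patients:** four sites (HT7, HT3, LU9, LU5), recorded for 5 minutes.
- **Moxibustion:** two sessions. In each, "LDF probes will be placed in three measurement sites", and "The measurement time points include 5 minutes before moxibustion, 15 minutes during moxibustion and 5 minutes after removal of moxibustion".

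Section 2.10 names the tests. For change over time: "Repeated measures ANOVA will be used to assess change in continuous variables before and after intervention". The paired t-test "will be used to compare the changes within the groups, whereas the independent samples t-test will be employed for comparisons between the groups". Skewed data go to non-parametric tests. The section ends with a single threshold for all of them: a P "value of less than .05 will be considered statistically significant".

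The hypotheses appear only in the Discussion. The first reads "we hypothesize that the change in microcirculatory characteristics of the Heart meridian between the healthy control group and CSAP group is more significant than" the corresponding change in the Lung meridian. The second expects a larger change at sites on the stimulated meridian than on the non-stimulated one.

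**The concern.** Both hypotheses are differences of differences. The first asks whether the CSAP-versus-control difference is larger on the Heart meridian than on the Lung meridian. The second asks whether the change from baseline is larger on the stimulated meridian than on the other. Section 2.10 describes within-group and between-group comparisons but never says that the Heart–Lung difference is itself the quantity tested. Applied site by site, those tests would show a P value below .05 at some sites and above it at others. That is not a test of whether two sites or meridians differ.

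The Discussion's wording, that one change is more significant than another, invites exactly that comparison of P values. Section 2.5 says the statisticians are blinded to the study protocol, so they cannot be relied on to infer the intended contrast from the Discussion.

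At stake is what the .05 means. With two primary outcomes, several sites, two sessions and three periods, and no designated contrast, it is the error rate of each test and not of either conclusion about specificity.

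**Working it through.** **No plan figure to reproduce.** The protocol states no familywise error rate or power. Its sample size rests on similar studies, so only 3 × 40 = 120 can be checked (section 2.2).

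**Inputs from the document.** α = .05 per test (section 2.10); 4 sites for CSAP versus control; 2 sessions × 3 sites × 3 periods for moxibustion (section 2.6.1); 40 per group (section 2.2).

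**Assumptions.** Tests are two-sided. The number of tests is not fixed by the document, so these counts of PU tests are tried:

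- 4: one CSAP-versus-control test per site.
- 10: those 4 plus one repeated measures ANOVA per session and site (2 × 3 = 6).
- 16: those 4 plus during-versus-before and after-versus-before at each session and site (2 × 3 × 2 = 12).
- 2: each Discussion hypothesis tested once.

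Correlation between tests is also unknown, so ρ = 0, 0.5, 0.7 and 0.8 are shown. The CSAP–control tests and the moxibustion tests are treated as independent blocks, because sections 2.2 and 2.6.1 describe three separate groups of 40.

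**Formulas.** For k independent tests, F(k) = 1 − 0.95^k. For k tests with common correlation ρ and c = 1.96, F(k, ρ) = 1 − ∫ φ(s) [Φ((c − √ρ·s)/√(1−ρ)) − Φ((−c − √ρ·s)/√(1−ρ))]^k ds. For two independent blocks with rates A and B, the total is 1 − (1 − A)(1 − B). The ANOVAs are approximated as two-sided z-tests.

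**Results: chance of at least one false positive**

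| ρ within block | 4 tests | 6 tests | 12 tests | 4 + 6 = 10 | 4 + 12 = 16 |
|---|---|---|---|---|---|
| 0 | 18.5% | 26.5% | 46.0% | 40.1% | 56.0% |
| 0.5 | 15.6% | 20.7% | 31.9% | 33.1% | 42.5% |
| 0.7 | 13.0% | 16.4% | 23.2% | 27.3% | 33.2% |
| 0.8 | 11.4% | 13.9% | 18.6% | 23.7% | 27.9% |

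Example at ρ = 0.5 with 16 tests: 1 − (1 − 0.156)(1 − 0.319) = 1 − 0.844 × 0.681 = 0.425.

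Two hypotheses tested once each: 1 − 0.95² = 9.75%.

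**Block assumption.** Section 2.6 and the Discussion place moxibustion in the healthy control group, while the Abstract and section 2.6.1 place it in the healthy intervention group. Those passages need reconciling. If the same people supplied both blocks, one common correlation across all tests would be the other extreme. At ρ = 0.5 that gives 28.7% for 10 tests and about 37% for 16, still far above 5%.

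**Cost of splitting α over two contrasts.** At 80% power, the t-based detectable effect with 40 versus 40 is 0.63 SD at α = .05 and 0.70 SD at .025. With 40 pairs it is 0.45 SD and 0.50 SD.

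**The case against.** The strongest reply is that the Discussion does state one comparative hypothesis per question, and the Abstract describes the first comparison too. That is right. It would be wrong to say that the protocol has no contrast in mind. What is missing is narrower: neither contrast is labelled primary, neither has a site, period or summary, and no listed test is attached to either.

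Four stronger readings are tempting, and the document does not support them:

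- **That any one positive site would count as evidence of specificity.** Both hypotheses are comparative. A lone CSAP–control difference at a Lung site would tell against the first, and a lone change at a non-stimulated site against the second. The percentages above are therefore rates for at least one false-positive site-level test, not for either specificity conclusion.
- **That a chance finding is likely.** In the table, only 16 fully independent tests pass 50%. Full independence is implausible for sites on one forearm and repeated periods in the same people.
- **That 16 is the planned number of tests.** Section 2.10 can equally be read as one ANOVA per session and site.
- **That the curve doubles the number of tests.** It has no stated numeric value and no test of its own, so how many tests it adds, if any, is unknown.

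It can also be said that multiplicity control is often left to an analysis plan, which is not shown here. That holds for the adjustment method. But which outcome is primary is a protocol matter, and here it is settled badly.

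Finally, the limitations call the study a pilot whose results need cautious interpretation. This softens the case for strict familywise control. It does not remove it, because the Discussion aims to verify specificity and the Conclusions promise high-quality evidence for choosing prescriptions.

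**Conclusion.** The point stands in limited form. The primary outcome is not operational, the two stated hypotheses have no designated test, and a flat .05 over site-level tests does not hold the error rate at 5%. Every count and correlation tried exceeds it: about 11–19% for the four CSAP–control tests, about 24–56% for 10 to 16 PU tests, and 9.75% for the two hypotheses alone. These figures depend on an assumed number of tests, assumed correlations and, for the 10- and 16-test figures, independence of the two blocks. They show the order of magnitude, not a property the document fixes. The more basic defect needs no arithmetic: separate site-level tests do not answer a Heart-versus-Lung question.

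**What to change.** Before any analysis, amend sections 2.7 and 2.10 as follows.

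1. Make mean PU over the stated recording window the sole primary outcome, and the blood flow curve descriptive.
2. For the first hypothesis, name the group-by-meridian contrast. For each participant, take mean PU at HT7 and HT3 minus mean PU at LU9 and LU5, then compare CSAP with healthy controls.
3. For the second, name the stimulated-minus-non-stimulated contrast in change from the 5-minute baseline at the two forearm midpoints, averaged over the two sessions, for one period named in advance. Both midpoints are recorded in both sessions, so each serves once as stimulated and once as comparison, giving one paired value per participant.
4. Report all site- and period-level results as estimates with 95% confidence intervals, without significance claims.
5. If one overall trial claim is intended, control the two contrasts by Holm at .05. If they are reported as two separate questions, this is optional. Analysing PU on a log scale is likewise a matter of choice.

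The cost is wording in the protocol, registry entry and analysis plan, with no new participants or measurements. Under Holm the smaller P value must be below .025. In the worst case the effect detectable with 80% power rises from 0.63 to 0.70 SD between groups and from 0.45 to 0.50 SD for the paired contrast.

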### Patient and public involvement

2.11

Patients or the public are not involved in the design, or conduct, or reporting, or dissemination plans of our research.

### Ethics and dissemination

2.12

The study is planned in accordance with the Declaration of Helsinki. Ethics approval (approval No: ZSLL-KY-2019-001A-01) has been obtained from the Ethics Committee of the Third Affiliated Hospital of Zhejiang Chinese Medical University. All the participants will be fully informed about this trial and given enough time to inquire about details involving the purpose, contents, benefits and potential risks of the study. Informed consent will be signed if they agree to participate.

The trial has been registered at Clinical Trial Registry with the identification code NCT04244812. The study findings will be disseminated through presentation at peer-reviewed journals.

## Discussion

3

By far, the biological characteristics of meridians has been investigated. Over the last few decades, results from many studies have suggested distinctive biophysical features of the meridians, such as high electrical conductance,^[18–20]^ nitric oxide levels,^[21,22]^ high transcutaneous CO_2_ emissions,^[23]^ acupuncture sensation patterns,^[24]^ and possible relationships with connective tissue.^[25,26]^ Nevertheless, the scientific evidence on the microcirculatory characteristics of meridians still needs further explosion by using modern scientific techniques.

In addition, the topic of acupoint/site specificity has received increasing attention in acupuncture research. According to the classical acupuncture theory, the effects of acupuncture are site specific, which are also supported by results from modern studies. For examples, Gao et al^[27]^ demonstrated that acupuncture stimulation of the ear had a more significant inhibitory effect on mean arterial pressure and heart rate than that of the lower leg and forearm. Minagawa et al^[28]^ also reported the site-specific, organ-selective effect of an epifascial acupuncture stimulation. Significant neuroimaging evidence of acupoint specificity of the vision-related acupoints was provided by Cho et al.^[29]^ However, no consensus has yet been reached on the existence of acupoint/site specificity.^[12]^

Therefore, we have designed an ongoing clinical trial to compare the microcirculatory characteristics of 2 specific meridians by using an objective assessment tool and verify the specificity between 2 specific meridians. The highlights and strengths of this study are presented as below.

First, to the best of our knowledge, this trial is the first study to compare the difference in microcirculatory characteristics of 2 specific meridians by using LDF. Previous studies^[30–32]^ have proved that LDF is a well-established technique to monitor microcirculation flux in acupuncture-related trials due to its non-invasiveness and real-time capability of measurements.

Second, our study design presents different comparisons to verify the specificity for the meridian-visceral association and site-to-site association between 2 specific meridians, which is a highlight. The theory of meridian-viscera association emphasizes the diagnostic and therapeutic values based on the mutual relation in physiology and the interaction effect in pathology between meridians and viscera. In details, visceral physiological functions and pathological changes will manifest in the corresponding meridians or the acupoints^[33]^ and the visceral disorders can be treated with the involved meridian and acupoints.^[34]^ A number of modern studies have confirmed the relatively specific relationship between meridians and viscera, and the modulating effect of acupoints/meridians for the visceral function^[35–37]^ On 1 hand, we hypothesize that the change in microcirculatory characteristics of the Heart meridian between the healthy control group and CSAP group is more significant than that of the Lung meridian. Thus, the specificity for the meridian-visceral association will be investigated by comparing the microcirculatory difference between the Heart and Lung meridians in the healthy control group and CSAP group. We present such a comparison (healthy control group vs CSAP group) to verify the sensitization phenomena of meridians under pathological circumstances as well as the specificity of meridian-visceral association.

On the other hand, we hypothesize that the change in microcirculatory characteristics in relevant sites of the stimulated meridian is more significant than that of the non-stimulated meridian in the healthy control group. Thus, the specificity for the site-to-site association will be explored by comparing the microcirculatory change between the Heart and Lung meridians by performing moxibustion in the Heart meridian and Lung meridian, respectively. It should be noted that moxibustion intervention is applied only in the healthy control group rather than the CSAP group. By such a study design and comparison, we attempt to confirm whether meridians are not only sensitized in pathological conditions but also activated in physiological state, which is an important issue to be solved in meridian researches.

To summary, based on rigorous experimental designs, the findings concerning the specificity between two specific meridians could contribute to the selection of appropriate acupoints and help optimize the therapeutic effect of acupuncture in clinical practice. It could bring important references to the study of meridian theory in modern researches.

Despite the highlights and strengths of this study, several limitations have to be addressed. First, the sample size is small. But as a pilot trial, the results of this study will provide evidence for the feasibility of this trial design as well as basic data for similar meridian studies in a large-scale study. It is expected to guide the design of a full-scale trial in the future. Second, the results should be interpreted in caution. A number of factors which can influence adequate interpretation of data must be considered.

## Conclusions

4

In conclusion, this protocol describes an ongoing clinical trial to compare the microcirculatory characteristics of different meridians by using LDF. Specifically, different comparison groups are designed to verify the specificity for the meridian-visceral association and site-to-site association between two specific meridians. The results of the meridian specificity will provide high-quality evidence for a better acupuncture prescription selection in clinical practice so as to improve the therapeutic effect of acupuncture.
